## Abstract

**Background:**

The changing landscape of the work environment, which often encompasses expectations of employees being continuously available, makes it difficult to disengage from work and recover. This can have a negative impact on employees’ well-being, resulting in burnout, depression and anxiety, among other difficulties. The current study will test the effectiveness of two different online interventions (i.e., cognitive behavioral therapy; CBT and mindfulness-based stress reduction; MBSR) on employees’ psychological detachment, burnout and other variables related to general (e.g., life satisfaction) and work-specific (e.g., work engagement) well-being.

**Methods/design:**

The study is designed as a randomized control trial with two intervention groups (i.e., CBT, MBSR) and a waitlist control group. Participants will be full-time employees from a wide range of organizations from Slovenia, who report moderate difficulties with psychological detachment from work and burnout and are not receiving any other form of treatment. The online interventions will encompass 12 sessions over 6 weeks (2 sessions per week); each session will include 1) an active audio-guided session and 2) home assignments, accompanied by handouts and worksheets. The study outcomes (i.e., psychological detachment, burnout, general and work-specific well-being), potential mechanisms (i.e., work-related maladaptive thinking patterns, mindfulness) and moderators (e.g., supervisor support for recovery) will be assessed immediately before and after the interventions (pre and post measurement) and 3 months after intervention completion (follow-up). Additionally, participants will fill out questionnaires for the assessment of the central mechanisms and study outcomes each week.

**Discussion:**

We expect that the CBT-based intervention will lead to greater improvements in psychological detachment from work and burnout compared to the MBSR and the waitlist control group. Additionally, we expect that the CBT-based intervention will also lead to greater enhancement of both general and work-related well-being.

**Trial registration:**

https://doi.org/10.1186/ISRCTN98347361 [May 19, 2020].

## Background

Today’s work realities are clearly different from those decades ago. With work carried out at any given time anywhere and managerial expectations to be available anytime, anywhere, employees frequently find it difficult to psychologically “switch-off” their work during non-work time. Therefore, recovery from work is increasingly difficult to achieve [1]. At the same time, employee reports of stress, work-family conflict, and burnout are a cause for concern. A recent representative study found, for instance, that around 25% of EU employees report work-related stress for all or most of their work time (e.g., [2]). One in ten employees reports that their work does not allow them to spend as much time with their families as they would like [3]. Additionally, data from the 6th European Working Conditions Survey show that in several European countries more than 10% of employees always feel exhausted at the end of the working day [4]. At the societal and organizational levels, these widespread concerns notably hamper productivity and are associated with major healthcare-related costs [5].

A lack of psychological detachment from work and employee well-being are clearly interconnected. According to the effort recovery model [6], a period of unwinding after exposure to job demands is necessary to replenish energy levels and start the next work day in an optimal psychophysiological state. If recovery after work is hampered over a longer period, employees will eventually face negative consequences in terms of well-being. A crucial condition for recovery is psychological detachment from work, which refers to “an individual’s sense of being away from the work situation” ([7], p. 579). Detachment encompasses mentally and emotionally disconnecting from work and refraining from work-related tasks such as checking e-mails, reading work materials, or completing unfinished tasks [8, 9]. In the present study, the focus is on the negative side of psychological detachment where one worries about upcoming work tasks, ruminates about past work experiences, or feels pressured (either internally or externally) into work-related tasks during non-work time [9, 10]. Previous studies have found that poor detachment from work is positively associated with exhaustion, burnout, poor sleep, and work-family conflict [9, 11, 12]. At the same time, a lack of detachment is negatively linked to work engagement, life satisfaction, and other general well-being indicators.

Several individual-oriented intervention studies have shown that the ability to detach from work and unwind at home can be taught (e.g., [13]). In particular, interventions that include elements of cognitive-behavioral therapy (CBT) and mindfulness were found to help employees to psychologically detach from work during non-work time [13–18]. In addition, such interventions contribute to the prevention of stress, negative affect [13], anxiety, and depression [17, 19] as well as sleep disturbances [16, 17]. Beneficial effects of CBT and mindfulness interventions for employees are evident not only with respect to general well-being, but also for work-related outcomes such as exhaustion and burnout [17, 20], work engagement [21], job satisfaction [20], work-family conflict, and work-family balance [22, 23]. While previous studies suggest that both types of interventions can be effective, interventions with CBT elements show more pronounced positive effects in terms of employee well-being [24].

Nevertheless, the development and implementation of effective interventions for employees still raise many different questions. First, intervention research needs to expand the understanding of why CBT-based and mindfulness interventions are effective and which mechanisms are responsible for the beneficial effects [14, 25, 26]. Especially in organizational settings where time constraints, logistical hurdles, and managerial attitudes can limit the widespread use of such interventions, additional knowledge about mechanisms of change is crucial [25, 26]. In fact, it has previously been argued that psychological intervention studies should shift their focus from the effectiveness of the treatment to understanding the underlying mechanisms and, consequently, informing theory [27]. In order to provide cost- and time-effective evidence-based workplace interventions, a more nuanced understanding of what elements can be dropped from interventions, and what elements are decisive ingredients is needed [28]. Improved mindfulness skills, such as paying closer attention to one’s momentary activities instead of ruminating about the past or worrying about the future, were found to act as mechanisms of change (or mediators) of the intervention effects among employees [14, 17]. Other potential mechanisms which help to increase psychological detachment and employee well-being have yet to be considered.

Second, intervention research needs to determine what type of intervention or protocol is superior and whether the proposed mechanisms of change are general (i.e., operating across interventions), intervention-specific, or non-existent. As CBT-based and mindfulness intervention studies focus on one or the other type of intervention, direct comparisons of effects in a workplace context are not yet possible [26]. The majority of studies follow either the Mindfulness-Based Stress Reduction (MBSR [29]) or the Mindfulness-Based Cognitive Therapy (MBCT [30]) protocol [25]. Mixed protocols such as MBCT, which combines CBT methods and meditative mindfulness practices, make it additionally difficult to draw conclusions about which mechanisms are responsible for intervention effects. While the MBSR protocol especially focuses on achieving a purposeful awareness of the present moment through different mediations exercises, the MBCT protocol additionally includes exercises that help to identify maladaptive thinking patterns, reframe, and replace them. Adding another layer of complexity, MBSR and CBT may be effective because of similar underlying mechanisms. Similar to CBT, MBSR is also proposed to disconnect the maladaptive links between the way people think, feel, and behave (i.e., a desynchrony effect [31]). MBSR and CBT thus, both enable disengaging from maladaptive thinking patterns and, in turn, achieving cognitive change [32, 33]. On the other hand, CBT may also increase mindful awareness and thus address a similar change mechanism as MBSR [34].

Finally, a detailed understanding of different organizational, individual, and intervention design factors that have the potential to alter intervention effects is needed [25, 26]. Tentative evidence suggests that CBT- and mindfulness-based interventions may be more effective for white-collar employees [14]. Organizational variables such as managerial support for recovery [35], a climate that supports segmentation between work and home [36] as well as the level of unfinished tasks [37] may also represent essential boundary conditions. In cases where the workplace does not favor psychological detachment from work, and the amount of work tasks does not permit it, intervention effects on detachment and well-being outcomes are likely to be attenuated. Considering individual factors, studies have discussed the role of treatment-by-baseline interactions in which individuals with different baseline levels of the variables of interest show different reactions to interventions [16]. Particularly those individuals who are more at risk with respect to well-being indicators have the potential to gain more from the intervention. Lastly, intervention design factors such as the length of the intervention, commitment to homework assignments, and training demands (i.e., the complexity of homework assignments) are likely to play a role in attenuating and accentuating CBT- and mindfulness-based intervention effects [14, 15].

### Objectives and hypotheses

In order to advance CBT- and mindfulness-based intervention research for employees, the objectives of the present randomized control trial are: a) to evaluate the effectiveness of a MBSR intervention on psychological detachment and well-being indicators; b) to evaluate the effectiveness of a CBT-based intervention on psychological detachment and well-being indicators; c) to compare the strength of the effects of both protocols; d) to determine which mechanisms are responsible for the intervention effects (i.e., mediators) and test whether these mechanisms are general or intervention-specific; e) to explore boundary conditions (i.e., moderators) which attenuate or accentuate intervention effects. To determine the decisive ingredient in CBT-based and mindfulness interventions, the CBT protocol will predominantly be aimed at identifying and changing maladaptive thinking patterns and associated behaviors. The MBSR protocol, on the other hand, will predominantly include exercises that focus explicitly on increasing present moment awareness by using established exercises that aim to improve mindfulness practices [14, 38]. Although research has found that both CBT and MBSR protocols are effective with respect to employee well-being [14, 17, 18, 24], we tentatively assume that the CBT protocol will be superior for most of the studied outcomes as it is theory-driven, well-researched, and empirically supported for a wide range of conditions including moderate to severe symptoms of several psychological disorders [39]. It may also be more appropriate for targeting an important underlying factor contributing to poor detachment and burnout (i.e., maladaptive thinking patterns) [40]. Moreover, interventions that include some form of CBT exercises along with other exercises are found to be most effective [17, 18, 22, 41]. More precisely, we hypothesize that the CBT-based intervention will lead to higher levels of psychological detachment from work directly after the intervention (T2) and at follow-up (T3) compared to levels prior to the intervention (T1) and to MBSR and control groups. Additionally, we assume that the CBT-based intervention will lead to enhanced (general and work-specific) well-being directly after the intervention (T2) and at follow-up (T3) compared to levels prior to the intervention (T1) and to MBSR and control groups. In line with previous studies (e.g., [41]), a wider range of general (life satisfaction, depression, anxiety, stress, positive and negative affect, sleep quality) and work-related well-being (work engagement, workaholism, work-family conflict) outcomes will be assessed. Along with psychological detachment from work, burnout also represents a primary outcome as both interventions will be adapted to the work context and conditions of high job demands.

In line with one of the main objectives, we will focus on (work-related) maladaptive thinking patterns and mindfulness as mechanisms of change behind both protocols. Maladaptive thinking patterns are inflexible, unreasonable, and negatively-valenced cognitions that may guide one’s attention toward work and may lead to excessive preoccupation with work-related tasks [40]. Within CBT, these maladaptive thinking patterns are labeled as negative automatic thoughts or cognitive distortions. Mindfulness, on the other hand, is defined as an aware and non-judgmental state of mind in which one’s attention is directed toward the present moment [14, 38, 42]. Given that CBT is primarily aimed at altering maladaptive thinking patterns and MBSR at increasing trait mindfulness, we assume mechanisms of change during our intervention will correspond to the main goal of each protocol. In other terms, we hypothesize that work-related maladaptive thinking patterns will act as a mechanism through which the CBT-based intervention will contribute to higher psychological detachment from work and improved well-being, and mindfulness will act as a mechanism of change for the MBSR intervention. Since the proposed mechanisms may not be intervention-specific [33, 34], we will also test whether maladaptive thinking patterns and mindfulness act as mechanisms of change in MBSR and CBT-based intervention, respectively. As authors have argued that the proposed mediators and outcomes should be monitored not only at the end but also during the intervention [27], we will measure work-related maladaptive thinking patterns, mindfulness, psychological detachment, and burnout levels also on multiple occasions during the intervention. We assume that we will be able to establish a timeline between the proposed mediators and outcomes with a decrease of maladaptive thinking patterns and an increase of mindfulness across the intervention weeks associated with the primary outcomes of interest.

As CBT-based and MBSR interventions will most likely not be equally beneficial for all participants, we will further explore the moderating role of several organizational, individual, and intervention design factors. More precisely, we will focus on variables that have the potential to attenuate the effects of the intervention, primarily on psychological detachment and burnout (supervisor support for recovery, segmentation supplies, unfinished tasks, and time pressure). In line with previous studies, we will also consider compliance with intervention exercises, completion of homework assignments, and satisfaction with the interventions as potential moderating variables.

## Methods/design

### Study design

The randomized controlled trial will follow the recommendations of the CONSORT (Consolidated Standards of Reporting Trials) group, which is considered a gold standard in clinical practice regarding devising interventions as well as their reporting [43]. The study design is depicted in Fig. 1. The study will take place between October 2020 and February 2021. In order to reach the target sample size, the second round of data collection will take place between January 2021 and May 2021, and additional rounds of data collection will be carried out if needed. Data collection in both intervention groups (i.e., CBT- and MBSR protocol) and the control group will be carried out immediately before (T1) and after the intervention (T2). During the 6-week intervention period, weekly questionnaires will be sent out to participants. The follow-up data collection will take place 3 months after the end of the intervention (T3). During T1, T2 and T3, participants will be asked to fill out questionnaires addressing all studied constructs, whereas the weekly questionnaire will only encompass the central mechanisms and primary study outcomes (i.e., work-related maladaptive thinking patterns, mindfulness, psychological detachment, and burnout). During the intervention period, participants from both intervention groups will receive e-mail notifications every Monday and Thursday with information about the assignments and exercises. The initial e-mail will include instructions on how to access the online platform with CBT and MBSR exercises. The notification every Monday will remind participants to fill out the weekly questionnaire before they start with the new exercise. All exercises from previous weeks will be visible on the online platform. Upcoming exercises will not yet be available to ensure that participants will not skip the activities or perform them in random order. The online platform will automatically monitor whether the participants followed the instructions and performed the respective exercises. In case of non-compliance, reminders will be sent out the following day. After the intervention, participants from the waitlist control groups will receive access to the online platform and all intervention materials, which they can perform in any order. They will receive weekly e-mails reminding them to perform the exercises and encouraging them to practice them. After the intervention, each participant will have the opportunity to request individualized feedback on his or her results.

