### Participants and recruitment

The participants will be recruited from various organizations in Slovenia partnered with the leading institution and through different media channels. The intervention will also be advertised through university newsletters and webpages as well as a well-known Slovenian mental health platform. Interested participants will be able to apply for the study via an online form. Although we will not specifically exclude any professions, employees with knowledge-intensive jobs and high-stress occupations will be primarily targeted [44]. The recruitment stage will begin in August 2020. Following previous intervention studies in the workplace context (e.g., [17, 18]), participants will be pre-screened for eligibility. They will have to meet the following inclusion criteria: 1) being aged 18 or above, 2) working a minimum of 40 h per week and currently not on sick leave, 3) ability to commit (at least) 2 h per week to the online training, 4) ongoing internet connection and computer accessibility, 5) reporting difficulties with psychological detachment from work and burnout at least to a moderate extent. Participants undergoing other forms of treatment (psychotherapy, pharmacotherapy) or who have a clinical diagnosis of mental illness will not be eligible to participate. They will, however, receive additional information on relevant health care services and a link to mindfulness and CBT exercises they can practice on their own. Those eligible to participate will receive detailed information about the intervention and an online informed consent form. Participants who will commit to the study will be randomly assigned to one of the three groups. Following the approach by Querstret and colleagues [17], block randomization based on gender will be used. Participants will be randomized within blocks in such a way that an equal number of females and males are assigned to each of the groups because women exhibit more rumination and difficulties detaching from work at home (e.g., [17]). In order to control for expectations about potential benefits of the interventions, participants will be blinded to the intervention. Both the CBT-based and the MBSR intervention will be advertised as occupational stress-reduction interventions. The participants assigned to the waitlist control group will only be asked to participate in the study and fill out the questionnaires. They will also receive information regarding the delayed starting date of the training.

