### Statistical analysis

#### Sample size calculation

The G*Power 3.1 software was used to determine the minimum number of participants that need to be recruited [64]. We set the expected effect size to medium (*f(V)* = .25), the probability of a Type I error to α = .05, the statistical power (1-β) to .95 and chose a two-way repeated measures MANOVA (multivariate analysis of variance) with time (3 levels: pre, post, and follow-up) as the within-subjects factor and group (3 levels: CBT, MBSR, and control) as the between-subjects factor as the main statistical test. Given these specifications, the required total sample size is 151 participants (approximately 50 participants per group). In case of non-adherence and/or drop-out, the total sample size of 98 participants (approximately 33 participants per group) suffice with a more standard power level of .80.

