#### Effect evaluation

The analyses will be carried out with SPSS [88] and Mplus [89]. The significance level used in the analyses will be .05. The main research questions (i.e., group differences in psychological detachment from work and burnout) will be analyzed with two separate two-way repeated measures analyses of variance (ANOVAs), with time as the within-subjects factor (3 levels: pre, post, follow-up) and group as the between-subjects factor (3 levels: CBT, MBSR, control), for each of the main outcomes separately. Significant interactions will be followed up with a simple effects’ analysis, using the Bonferroni correction to adjust for multiple testing.

The effects of the intervention on the secondary outcomes (i.e., general and work-related well-being) will be analyzed with a two-way repeated-measures MANOVA, with time as the within-subjects factor and group as the between-subjects factor. This analysis is contingent upon moderate correlations between the dependent variables [90]. Therefore, we will first examine correlations between the secondary outcome variables. Significant interaction effects will be followed-up with ANOVAs for each of the dependent variables and a discriminant descriptive analysis to further examine the effects. The moderation (i.e., supervisor support for recovery, work-home integration supplies, unfinished tasks, time pressure) and mediation (i.e., mindfulness, work-related maladaptive thinking patterns) effects will be analyzed using the PROCESS macro for SPSS [91]. T2 measures of the studied mediators will be utilized in these analyses. In order to explore both; the inter-individual variability and the intra-individual patterns of change trajectories in the mechanisms and the main outcomes during interventions, growth curve analyses will be conducted using data from the weekly questionnaires.

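### The trial is planned in at least two rounds about three months apart, but the primary ANOVAs have no round term, so any round difference in the time course goes into error: a modest loss of precision, not bias.

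*Protocol article*

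**What the plan says.** **Timing (Study design).** The first run is dated: "The study will take place between October 2020 and February 2021". A further run is planned so that enough participants are enrolled: "the second round of data collection will take place between January 2021 and May 2021". Beyond these two, the number of runs is left open. The programme lasts six weeks, and "The follow-up data collection will take place 3 months after the end of the intervention (T3".

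**Allocation (Participants and recruitment).** The article forms its blocks by gender and explains the aim: "Participants will be randomized within blocks in such a way that an equal number of females and males are assigned to each of the groups". Gender is the only blocking factor named. Whether blocks are closed at the end of a round is not stated.

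**Primary analysis (Effect evaluation).** Detachment and burnout are each analysed by a two-way repeated measures ANOVA "with time as the within-subjects factor (3 levels: pre, post, follow-up) and group as the between-subjects factor (3 levels: CBT, MBSR, control". No further term is named, and round does not appear among the moderators, control variables or background variables.

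**The concern.** The time factor treats T1, T2 and T3 as the same three occasions for everyone. In calendar terms they are not: one round starts about October and the next about January. The article itself treats workload as relevant to detachment and burnout. Its Background expects weaker effects where the amount of work does not permit detachment, and it lists unfinished tasks and time pressure as possible moderators. If workload differs between the two periods, the untreated course from pre to post could differ between rounds as well.

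A time-by-group model has nowhere to put such a difference except the residual. At stake is some power for the group-by-time test. This matters most at the 98-participant fallback, which the article relies on if participants drop out and which has no slack at .80.

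**Working it through.** **1. Calendar check.** October plus 6 weeks plus 3 months is about mid-February. January plus 6 weeks plus 3 months is about mid-May. Both agree with the stated periods.

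| | T1 | T2 | T3 |
|---|---|---|---|
| Round 1 | about October | about mid-November | about February |
| Round 2 | about January | about mid-February | about May |

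The rounds overlap in the calendar, but the same time point falls about three months later in round 2.

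**2. The plan's own sample size.** The inputs, from Sample size calculation, are "expected effect size to medium (*f(V)* = .25", alpha .05, 3 groups and 3 times. For the within-between interaction (Pillai), df1 = (3 − 1)(3 − 1) = 4, df2 = 2(N − 3) and λ = N × 2 × 0.25².

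- N = 151: λ = 18.875, df2 = 296, power .950.
- N = 98: λ = 12.25, df2 = 190, power .800.

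Both stated figures reproduce.

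**3. Effect of leaving round out.** Let δ be the between-round difference in untreated change, in SDs of the outcome, and p the share of participants in round 1. The variance added to the change score is p(1 − p)δ², which is δ²/4 for two equal rounds. The within-round variance of the change is 2(1 − r). The document gives neither δ nor r. I assume δ = 0.3 to 0.5 and r = .6, so 2(1 − .6) = 0.8.

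- δ = 0.3: 0.0225 / 0.8 = 2.8% more variance; √1.028 = 1.014, so the SE rises by 1.4%.
- δ = 0.5: 0.0625 / 0.8 = 7.8% more variance; √1.078 = 1.038, so the SE rises by 3.8%.

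Dividing λ by the inflation factor, with the same inflation assumed on both time contrasts, gives:

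| δ (assumed) | Inflation | Power, N = 151 | Power, N = 98 |
|---|---|---|---|
| 0 | 1.000 | .950 | .800 |
| 0.3 | 1.028 | .944 | .788 |
| 0.5 | 1.078 | .932 | .766 |

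Equal rounds are the least favourable split, because p(1 − p) is largest at p = .5. With an 80:20 split, power at N = 151 is .946 to .939.

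**4. Effect of modelling round.** With two rounds, df2 falls from 2(N − 3) to 2(N − 4). Power stays at .950 for N = 151 and .800 for N = 98.

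**5. Validity of the test without a round term.** This was simulated with N = 150, two rounds and 4,000 runs per setting. Here d is the round difference in SDs of the change contrast, and δ = 0.3 to 0.5 corresponds to d of about 0.34 to 0.56 (δ/√0.8). With d from 0 to 1.0 and round left to chance across arms, type I error was .0465 to .052. With rounds exactly balanced across arms but not modelled, the test became conservative: .043 at d = 0.5 and .019 at d = 1.0. With a round term, type I error was about .05 and power about .95 throughout.

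**The case against.** The strongest reply is that this is a small refinement resting on an assumption. No seasonal difference is documented, the round sizes are not given, and equal rounds are the worst case. At the target of 151 participants and 95% power, no conclusion is threatened. Time counted from the start of the intervention is standard, workload is measured in part through time pressure and unfinished tasks, and an analysis plan not shown here could add a round term. Most of this stands and sets the size of the point. It does not remove the point, because Effect evaluation states the factors of the primary models explicitly and round is not among them.

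Three stronger readings are tempting, and the documents do not support them.

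- **Bias.** A reader might infer that uneven arm sizes within a round would bias the arm comparison. Participants are randomised, so such unevenness is chance error that the test already covers, as the simulated type I error shows.
- **Faulty allocation.** A reader might infer that the rounds are not randomised separately. The article does not say so. People who join for a January start are presumably allocated when they join, and gender-blocked allocation of each batch would roughly balance the arms within it. Such operational detail is commonly left to a full protocol.
- **A hidden round-specific effect.** A reader might want each round analysed in its own right. The trial asks no round-specific question, and about 50 per group over two equal rounds leaves about 25 per arm per round, so a display by round would be mostly noise.

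**Conclusion.** The point holds as one of precision. At least two rounds are planned with T1 in different seasons, and the primary models as stated send any round-by-time difference into the residual. For an assumed difference of 0.3 to 0.5 SD, two equal rounds and a T1-T2 correlation of .6, the loss is about 0.6 to 1.8 power points at N = 151 and about 1.3 to 3.5 at N = 98. In the second case the fallback no longer reaches its stated .80. If the rounds do not differ, nothing is lost. The absence of bias and of type I error inflation rests on all three arms running concurrently in each round.

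**What to change.** In Effect evaluation, add round and round by time to both primary ANOVAs, with one level per round actually run. In Participants and recruitment, state that the gender-blocked allocation to the three arms is done within each round. Balance alone would not be enough, because balanced rounds that are not modelled still leave their variance in the residual.

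The cost is one sentence in each section. With two rounds the model gives up one between-subject and two within-subject degrees of freedom, and slightly more for each further round. Round is known for every participant, so no new data are needed. Because the number of rounds is open, settling this now also avoids a later choice made with the data in view. A descriptive display by round is optional.
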